#### a) Clinical assessment

The choice of clinical parameters is generally based on the ICHOM standards. Clinical evaluation will be carried out using the modified KSS and its functional component. The KOOS will be used to assess pain, symptoms, activities of daily living, sport and recreation and knee related quality of life.

#### b) Physical activity level

Physical activity (PA) level during the 7 days prior to the experiment and during the experiment will be recorded using an activity monitor (ActiGraph GT3X+, Pensacola, FL, USA; e.g. number of steps taken, Kcal, PA intensity). The ActiGraph is widely used in scientific research and has been shown to be highly reliable, valid and responsive. The ActiGraph will be attached to a waist belt and placed on the subject's right side. Tracking PA levels will allow us to monitor regular PA level and if participants indeed did not perform demanding physical activities on the days prior to test days according to the experimental instructions.

#### c) Walking stress test

Before the walking stress test, participants will rest for 60 minutes, and blood samples will be taken at the end of the 60-minutes resting time ( $t_0$ ). They will then walk with either one of the

loading conditions for 30-minutes on the treadmill (with the walking speed determined in baseline day) followed immediately by another blood sample ( $t_1$ ). The inertial sensor based gait analysis system RehaGait® is attached to the subject's lower extremity to record their joint kinematic patterns during the walking exercise. Subjects will then rest for 3.5 hours, and blood samples will be taken at 30-minutes of the resting time ( $t_2$ ) and after two additional 90-minute resting intervals ( $t_3$  and  $t_4$ ; Figure 1). Subjects movements are recorded during the whole test days using the AchtiGraph activity monitor. The unloading system comprises a steel frame, weights, a pulley system and an unloading harness (h/p/cosmos airwalk®, h/p/cosmos sports & medical GmbH, Nussdorf-Traunstein, Germany). The loading system consists of an adjustable weight vest in which weights are applied in front and in the back equally. With this system we are able to decrease the participant's BW dynamically to 80% and increase the BW to 120%, for the whole 30-minutes stress test.

#### *d) Modulating ambulatory load*

Ambulatory load is modulated using a load modulation framework on an instrumented h/p/cosmos treadmill (h/p/cosmos, Zebris FDM-T, Isny, Germany; 7168 sensors; area, 1.5 \* 0.5 m; range, 1–120 N/cm^2; precision, 1-120 N/cm^2 ± 5%; sampling rate, 120 Hz). The magnitude of ambulatory load during the walking stress test will be calculated as GRF impulse times the number of steps taken during the walking stress test. In the reduced load condition, we will reduce ambulatory load using an unloading system comprising a steel frame with an unloading mechanism attached to an instrumented treadmill. Weights corresponding to 20%BW of each participant will be set on an unweighting pressure gauge that controls a pneumatic cylinder attached to a compressor and a pulley a pulley system with minimal friction through an unloading harness to facilitate targeted 80% weight bearing throughout the entire gait cycle (h/p/cosmos airwalk®, h/p/cosmos sports & medical GmbH, Nussdorf-Traunstein, Germany). In the increased load condition, we will increase ambulatory load using an adjustable weight vest where approximately equal weight will be applied in the front and back. The added weight will total 20%BW for each participant to facilitate targeted 120% weight bearing throughout the entire gait cycle.

#### *e) Ground reaction force*

The walking stress test will be performed on an instrumented treadmill with an embedded plantar pressure plate (h/p/cosmos, Zebris FDM-T, Isny, Germany; 7168 sensors; area, 1.5 \* 0.5 m; range, 1–120 N/cm^2; precision, 1-120 N/cm^2 ± 5%; sampling rate, 120 Hz). The vertical ground reaction impulse (area under the vertical GRF curve) times the number of steps taken during the walking stress test will be calculated. This measure will be used as surrogate measure for ambulatory load because tibiofemoral force is strongly correlated with walking speed and treadmill reaction forces.

#### *f) Joint kinematics and kinetics*

For the walking stress test, an inertial sensor system (RehaGait®, Hasomed GmbH, Magdeburg, Germany) will be used to collect joint angle curves at the ankle, knee and hip. This system comprises seven inertial sensors attached bilaterally on the lateral aspects of the shoes, the lower and upper leg, and on the pelvis. Each sensor contains a 3-axial accelerometer, gyroscope and magnetometer. Linear acceleration, angular velocity and the magnetic field are recorded at 400 Hz. All raw data can be exported, and the system calculates spatiotemporal gait parameters and joint kinematics (foot, ankle, knee, hip). In our previous studies, we found very good to good reliability and good agreement with kinematic data obtained with the Vicon® system. This data will be used to monitor joint kinematics for the three loading conditions to ensure that the general gait patterns remain the same among conditions and could be included in our statistical models if patterns change between conditions.

To compare the ankle, knee and hip kinematics and kinetics between subjects with ACL injury and subjects with healthy knees gait analysis will be carried out on the baseline day after the MRI was taken. The subjects will perform an instrumented gait analysis on a treadmill with an

embedded plantar pressure plate (h/p/cosmos, Zebris FDM-T, Isny, Germany; 7168 sensors; area, 1.5 \* 0.5 m; range, 1–120 N/cm^2; precision, 1-120 N/cm^2 ± 5%; sampling rate, 120 Hz) and on an overground walkway with two embedded force plates (Kistler force plate 9260AA6, Kistler AG, Winterthur, Switzerland; sampling rate 2400 Hz). Further, participants will be asked to perform two 30-second unipedal stance trials. Simultaneously with the plantar pressure or force data, kinematic and electromyographic (EMG) data will be collected using a 9 camera Vicon system (Vicon, Oxford, UK; frame rate 120 Hz) and a 12 channel EMG system (myon AG, Schwarzenberg, Switzerland, sampling rate 2400 Hz). To assess 3D joint angles, reflective markers will be placed on predefined anatomical landmarks on the pelvis and lower legs. Surface electrodes will be placed bilaterally on the gluteus medius, vastus medialis and lateralis, semitendinosus, tibialis anterior, and gastrocnemius medialis muscles following the guidelines of the SENIAM project (Surface ElectroMyoGraphy for the Non-Invasive Assessment of Muscles). Participants will then walk for 2 minutes at 0% slope at their preferred walking speed and at 1.2 m/s. For all conditions, kinematic, EMG and pressure data will be recorded. Subsequently, the treadmill speed will be increased to preferred running speed and a running speed of 2.2m/s, and data for two times 30 seconds running will be recorded. Subjects will then complete overground walking trials in their own shoes on the walkway with embedded force plates. Participants will be asked to perform a single leg hop to assess whether their knee provides adequate stability for three safe single leg hops on maximal distance.

Maximum flexion, extension and rotation angles and joint moments will be computed using the Biomove software (Stanford University). Intensity of the electromyographic signals of walking trials will be normalized to those for maximum voluntary contraction using a dynamometer (Biodex System 4 Pro: Biodex Medical Systems, Shirley, NY, USA).

#### *g) Heart rate monitoring*

To assess and compare the cardiovascular stress subjects experience during the walking stress tests the heart rate will be measured. Therefore, subjects will be asked to wear a heart rate monitor (Polar m400, Polar Electro Europe AG, Steinhausen, Switzerland) with a chest strap Polar H7, Polar Electro Europe AG, Steinhausen, Switzerland). From minute 40 to 42 in the first resting period the resting heart rate will be recorded. During the walking stress test until 10 minutes after the stress test, heart rate will be recorded. Mean heart rates will be used to compare the cardiovascular stress between the three loading conditions.

#### *h) Biological assessment*

Venous blood samples (5ml each) will be obtained from the antecubital vein at each evaluation. A vein catheter (Vasofix® Safety PUR 20G, B. Braun Melsungen AG, Melsungen Germany) will be placed during the rest period before the first blood sample at  $t_0$  (Figure 1) and will stay there for the entire experiment (4.5 hours). After every blood sample, the catheter will be flushed with 10 ml isotonic saline solution (0.9% NaCl) to prevent plugging through clotting blood. The first 3 ml of every sample will be discarded to avoid dilution through the prior injected saline solution. Then the blood samples clot in the blood tubes (S-Monovette® 7.5ml Z-Gel, Sarstedt AG, Nümbrecht, Germany) for 30 minutes. Subsequently, they will be centrifuged (Sarstedt AG & Co SMC6) for 15 minutes at 2016 g and stored in the fridge (4°C) for no longer than 2 h until separation in aliquots at the Laboratory for Functional Biomechanics and frozen (-80°C). The blood sample at the 24-month follow up will be taken immediately after the MRI using a needle (Venofix® Safety 21G, B. Braun Melsungen AG, Melsungen Germany) and a tube (S-Monovette® 7.5ml Z-Gel, Sarstedt AG, Nümbrecht, Germany). Subsequent blood processing will be the same as for the baseline samples.

The concentration of serum biomarkers (IL-6, COMP, MMP-3, MMP-9, PGR-4, and ADAMTS-4) will be determined using commercially available ELISAs. Investigators will be blinded to the samples, which will be analyzed in duplicates and in random order. Differences due to inter-assay variation will be eliminated by comparing concentrations within subjects and testing all samples of any subject on the same plate. All blood analysis will be carried out by a professional service

(TecoMedical). The service provider will not receive any information on the samples other than the subject code and random sample numbers to ensure that all samples of the same subject will be placed on the same plate. The change in blood markers of articular cartilage will be calculated as the serum concentration after the walking exercise normalized to the serum concentration before the walking exercise.

#### *i) Tissue status*

Advanced MRI techniques offer quantitative assessment of macromolecular changes to the cartilage matrix. T2 relaxation time mapping has demonstrated some ability to track cartilage quality in OA, and T2 relaxation times are elevated in patients following ACL injury as early as 6 months after injury. Moreover, we have previously used MRI data to study the effect of unloading during bed-rest on cartilage morphology of in vivo tibiofemoral cartilage. Here, we will use T2 relaxation time as surrogate measure for assessing cartilage tissue status. MRI of both knees will be obtained using a 3T MR scanner (Prisma, Siemens Healthineers, Erlangen, Germany). For MRI measurements, subjects will be positioned supine and entered feet first. Each knee will be scanned separately. The knee will be centered in a dedicated knee coil, the popliteal fossa padded, allowing a slight knee flexion. The articular cartilage of the tibiofemoral joint will be imaged in the coronal plane. Imaging will be performed with a custom 12 minute 3D DESS sequence (echo time FISP S+ (TE S+)= 4.85msec, echo time PSIF S- (TE S-)= 4.85msec, repetition time (TR)=16.99msec, flip angle (FA)=15°, field of view (FOV)= 160 mm^2, slice thickness (ST)= 1.5 mm, matrix (RO x PE) 512 x 512; pixel size (PS)= 0.31 x 0.31mm^2, approx. 12 min). MRI segmentation will be done by an independent company (Chondrometrics GmbH medical data processing, [name], Germany) using their custom software (WORKS 3.0). The service provider will not receive any information on the images other than the subject code and random sample numbers to ensure that all samples of the same subject will be assessed in the same evaluation session. To measure differences in cartilage thickness in the tibiofemoral weight bearing regions, the tibiofemoral contact areas in the femoral cartilage will be divided into three functional weight bearing regions for each condyle based on the knee flexion angle during walking. The average thickness will be calculated for the weight bearing regions on the femur and tibia. T2 relaxation time is used as surrogate measure to assess cartilage tissue status. Cartilage degeneration will be assessed as the difference in T2 relaxation times and cartilage thickness between baseline and 24-month follow-up, respectively. The articular cartilage of the knee joint will be defined as normal if the cartilage thickness is preserved, no cartilage signal alterations and no superficial and deep cartilage defects or fissures are present.

#### *j) Other parameters*

Information regarding treatment (conservative or operative), time since injury, time of operation (if applicable), duration of physiotherapy, time of return to work, time of return to sport, or type of sports before injury will be recorded from the patient file.

### **3.4 Withdrawal and discontinuation**

Participants will be excluded if they withdraw their informed consent or do not follow the instructions given in the participant information. Data collected (clinical, biomechanical, biological) before withdrawal or discontinuation will be included in subsequent analyses to account for potential data bias. It is not possible to anonymise data in case a subject withdraws their consent to participate, and hence all data collected before withdrawal will be still be coded.

## 4 STATISTICS AND METHODOLOGY

### 4.1. Statistical analysis plan

All statistical analyses will be performed in Stata 15 (StataCorp LLC, College Station, Texas). In addressing the primary objective we will make use of the following variables:

- measurements of the blood markers at the five time points  $t_0$ ,  $t_1$ ,  $t_2$ ,  $t_3$  and  $t_4$  under the three conditions;
- the actual ambulatory load at each condition as determined by the biomechanical assessment;
- age of the participant;
- tissue status at baseline: T2 relaxation time and cartilage thickness;
- inflammation status at baseline.

We will start with an initial data analysis to inform the following research question driven analyses without touching these questions. The following aspects will be addressed:

- The marginal distribution of all variables.
- The association between the factors age, T2 relaxation time, cartilage thickness and inflammation.
- The typical course over time for each biomarker in order to define two (or more) outcomes reflecting the initial change ( $t_1$  compared to  $t_0$ ) and the following movement back to the initial level (course from  $t_1$  over  $t_2$  to  $t_4$ ).
- Variance heterogeneity and normality of residuals over time.
- Linearity of change in outcomes in dependence on ambulatory load.
- Variance heterogeneity of the outcomes in dependence on ambulatory load, age, tissue status and inflammation status.
- Correlations across biomarkers with respect to original measurements and outcomes.
- Characterization of the bivariate distribution of the two outcomes.

The research question will be addressed by the following sequence of analyses:

1. We will investigate the sensitivity of each outcome to the change in ambulatory load as well as the biological variation of the corresponding slope by a mixed model with the intercept and load as fixed and random factors. We will report:
  - the sensitivity of each biomarker to an ambulatory load, i.e. the population mean and population variation of the initial change at a load of 100%;
  - the sensitivity of each biomarker to a change in ambulatory load, i.e. the population mean of the slope of the regression of the initial change on the ambulatory load; and
  - the biological variation of these slopes.In addition, the results will be stratified by age, tissue status and inflammation.
2. We will investigate the effect of age on the slope for each outcome by a mixed model with intercept, load, age and the interaction between age and load as fixed effects and intercept and load as random effects.
3. We will investigate the effect of tissue and inflammation status (in addition to age) on the slope by a mixed model with intercept, load, age, tissue status, inflammation status and the interaction between the load and age, tissue status and inflammation status, respectively, as fixed effects and intercept and load as random effects. In dependence of the correlation between T2 relaxation time and cartilage thickness we will fit a separate model for both aspects of tissue status or a joint model.
4. We will investigate the correlation between the slopes for the two outcomes by corresponding joint mixed models and investigate also a dependence of the correlation on age, tissue status and inflammation status.
5. We will investigate the correlation of the slopes across the five different biomarkers by corresponding joint mixed models.

To allow simple comparisons of effects across the different biomarkers we will rescale all biomarkers to a median level of 100 at  $t_0$  under 100% intended ambulatory load. The dependence of the slope on age, tissue status and inflammation status will be expressed as the expected slope at selected values, e.g. lower and upper 10% population percentiles. The value of these factors will be depicted by the explained biological variation. To take the joint investigation of five – however probably correlated – biomarkers into account, we will use a reduced significance level of 0.025. Further explanatory and hypotheses generating analyses are planned with respect to new definitions of potential markers (e.g. ratios between two markers) or alternative definition of explaining factors (e.g. the three single inflammation markers).

With respect to the secondary objective, we will make use of additional clinical outcomes measured both a baseline and at the 2-years follow up. The primary outcome will be the change in T2 relaxation time. Secondary outcomes are the kinematics and kinetics in the initial gait analysis and single leg hop, the change in cartilage thickness, KOOS score, modified KSS score and physical activity. The distribution of the outcomes will be depicted in an initial data analysis. The research questions will be addressed by the following sequence of analyses:

1. We will investigate for each biomarker the associations of the individual slope with the clinical outcomes by a corresponding regression model focusing on effect sizes and explained variation.
2. We will investigate the independent prognostic value of the individual slopes for each biomarker by corresponding adjustments, first for age and then also for tissue status and inflammation.
3. We will investigate a potential effect modification by physical activity by adding corresponding interactions terms to the regression models.
4. In case the individual slopes do not carry independent prognostic value, we will investigate their mediation effects on the path from age (or age, tissue status and inflammation) towards the clinical outcome.
5. In case of independent prognostic value of the individual slopes for several biomarkers, we will also consider the amount of independent prognostic information by considering a model with all these biomarkers as covariates.

In all regression models the baseline value of the clinical outcome will be included as covariate. Since the individual slopes are estimated and we can assess their standard error, we will correct for this measurement error using regression calibration.

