### **3.3 Study procedures**

Each subject participating in this study undergoes a recruitment and information process that will last over approximately 1 month. The data collection (baseline day 1 and test days I, II and III) will happen on 4 different days within 1 month and with at least 1-day break between the test days (Figure 1). The follow-up will be scheduled 24 months after the baseline measurement (Figure 2). On the baseline day, the participant will complete two questionnaires (KSS, KOOS) concerning the health of their knees. Further, subjects will be clinically assessed by an orthopaedic surgeon, participants with childbearing potential will undergo a pregnancy test, and an MRI of both knees and gait data at least 7 days prior to the experiment will be recorded. Tissue status will be determined by the T2 relaxation time and thickness of weight bearing knee cartilage. Participants will be asked to wear an activity monitor (ActiGraph GT3X+, Pensacola, FL, USA) for 7 days prior to the first test day.

Each participant will complete the walking stress test with repeated blood sampling on three test days with at least 24 hours without physical activity before each test day (Figure 1; always at the

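### The primary slope models use the same-day resting level t0 only to normalise the response; adding it as a within-person covariate costs one coefficient and may sharpen the slopes

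*Protocol*

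**What the plan says.** Section 3.3 has each participant "complete the walking stress test with repeated blood sampling on three test days". Section 3.3 c) places the first sample of each test day, t0, before the walk: "blood samples will be taken at the end of the 60-minutes resting time". Every post-walk value therefore has its own same-day resting value.

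Section 3.3 h) defines the marker change as the "serum concentration after the walking exercise normalized to the serum concentration before the walking exercise". Section 4.1 lets the initial data analysis define "two (or more) outcomes reflecting the initial change" (t1 against t0) and the later return towards the starting level.

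The model terms are then listed. Step 1 is a "mixed model with the intercept and load as fixed and random factors". Step 2 is a "mixed model with intercept, load, age and the interaction between age and load as fixed effects and intercept and load as random effects". Step 3 adds tissue status, inflammation status and their interactions with load. No step contains t0 as a covariate. The rescaling to a median of 100 at t0 is a change of units and adjusts for nothing at the level of person and day.

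For the secondary objective, section 4.1 states: "In all regression models the baseline value of the clinical outcome will be included as covariate". That rule concerns the clinical outcome, not the marker.

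**The concern.** Dividing by t0, or subtracting it, assumes that a person's t0 deviation on a given day carries over in full to t1. A shift shared by both samples cancels. A shift in t0 alone does not, and with one t0 sample per day it goes straight into that day's response. Testing all of a subject's samples on one plate removes inter-assay differences, but intra-assay error remains; section 7.1 plans to estimate it and gives no value.

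Each slope rests on three responses, so this noise adds to the slope's error variance. At stake is precision for Hypotheses 1.1 to 1.3, for the estimated biological variation of the slope, and for the individual slopes carried into the secondary objective. Load order is randomised and t0 precedes the walk, so a within-person t0 deviation is independent of load. Adjusting for it does not bias the load interactions.

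**Working it through.** **Inputs from the protocol (section 4.1, Sample size calculation).** N = 96. Stated powers for the interaction of load with one covariate are 71% (slope SD 3.7, 50% of slope variation explained), 85% (SD 7.4, 25%) and 89% (SD 11.1, 20%). Stated standard errors of the estimated slope SD are 1.87, 1.27 and 1.24. The significance level for the primary objective is 0.025 (taken as two-sided).

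**Not in the protocol.** The residual variance, the within-person day-level correlation ρ of t0 and t1, and the ratio k = SD(t1)/SD(t0) at that level. These are assumed or back-solved.

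**Effect of the covariate on error variance.** In units of the day-level variance of t0:
- change score: k² + 1 − 2ρk
- with t0 as covariate: k²(1 − ρ²)
- factor c = k²(1 − ρ²)/(k² + 1 − 2ρk)

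The change-score variance exceeds the adjusted one by (1 − ρk)². The gain is therefore never negative and is zero exactly when ρk = 1. For k = 1, c = (1 + ρ)/2.

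**Reproducing the stated powers.** Let τ be the slope SD, p the explained share and s² the slope error variance. Since s² is not printed, two calibrations were used.

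*Calibration A, level 0.025.* r² = pτ²/(τ² + s²); power = Φ(atanh(r)·√93 − 2.241). Solving for the three stated powers gives s² = 72.4, 73.0 and 84.0. Check at SD 3.7: r² = 6.845/86.1 = 0.0795, r = 0.282, Φ(2.795 − 2.241) = 71%. These s² values do not fit the protocol's other figures. Using SE = √[(2/95)(τ² + s²)² + (2/96)s⁴]/(2τ), they imply 2.20, 1.44 and 1.46, against the stated 1.87, 1.27 and 1.24.

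*Calibration B, from the stated standard errors.* The same SE formula back-solves to s² = 60.4, 60.1 and 57.6; s² = 60 returns 1.86, 1.27 and 1.26. With power = Φ(√(Np)·τ/√(τ²(1 − p) + s²) − z), s² = 60 gives 71.2, 84.9 and 90.1% at a two-sided level of 0.01 (z = 2.576), but 81, 91 and 95% at 0.025.

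Neither calibration fits every printed figure, so both are shown.

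**After the change** (s² multiplied by c), power in % at slope SD 3.7 / 7.4 / 11.1:

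| k | ρ | c | Calibration A | Calibration B |
|---|---|---|---|---|
| – | before | 1 | 71 / 85 / 89 | 71.2 / 84.9 / 90.1 |
| 1 | 0.3 | 0.65 | 87.0 / 92.8 / 93.7 | 88.7 / 93.0 / 94.2 |
| 1 | 0.5 | 0.75 | 82.3 / 90.7 / 92.4 | 83.8 / 90.9 / 93.1 |
| 1 | 0.7 | 0.85 | 77.7 / 88.5 / 91.1 | 78.7 / 88.5 / 91.9 |
| 1 | 0.9 | 0.95 | 73.2 / 86.2 / 89.7 | 73.6 / 86.1 / 90.7 |
| 1.2 | 0.7 | 0.966 | 72.4 / 85.8 / 89.5 | 72.8 / 85.7 / 90.5 |
| 1.4 | 0.5 | 0.942 | 73.5 / 86.4 / 89.8 | 74.0 / 86.3 / 90.8 |
| 1.4 | 0.7 | 1.000 | 71.0 / 85.0 / 89.0 | 71.2 / 84.9 / 90.1 |

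Worked cell (k = 1, ρ = 0.5, SD 3.7, calibration B): s² = 60 × 0.75 = 45; √48 × 3.7/√(6.845 + 45) = 25.63/7.20 = 3.56; Φ(3.56 − 2.576) = 83.8%.

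When t1 varies less than t0, the gain is larger. At k = 0.8 and ρ = 0.7, c = 0.64 × 0.51/(1.64 − 1.12) = 0.628, and power at SD 3.7 is about 88% (A) or 90% (B).

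If s² = 60 is paired with the protocol's level of 0.025, then k = 1 and ρ = 0.5 move power from 81/91/95% to 91/95/97%.

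**Simulation check** (3000 repetitions, N = 96, level 0.025, s² = 73, k = 1). At ρ = 0.5, power rose from 73/85/91% to 83/91/93%; at ρ = 0.7, from 73/84/91% to 78/88/92%. The mean interaction estimate matched the true value with and without the covariate.

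No figures are given for the three-covariate simulation. The closed form does not reproduce it (77% and 94% under calibration B, against the stated 70% and 80%).

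**The case against.** A ratio analysed with random intercept and slope is a valid model, and nothing in the protocol is contradictory here. Section 4.1 leaves the exact outcomes to the initial data analysis, and a precision covariate is often settled in a separate analysis plan. The first part stands: this is an improvement, not an error. The second stands only in part. The outcome's scale is open, but the model terms are listed one by one and t0 is not among them.

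The gain rests on two quantities that the protocol does not give. If t1 is that day's t0 plus independent response noise, then ρk = 1 and there is nothing to gain. The largest gains also fall at slope SD 3.7, while the protocol expects a substantially larger variation. Both points stand and limit the claim.

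A reader might infer that the stated 71/85/89% are too high. The documents do not support that. If the pilot residual variance came from the same change outcome (an assumption), the stated powers already include the t0 noise. The mismatch between the printed standard errors and level 0.025 rests on a back-solved s² and is not evidence on this point.

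A reader might also see an inconsistency with the baseline rule for the secondary objective. That rule adjusts a 24-month change across persons, whereas the primary models compare days within a person. It is an analogy at most. The regression calibration planned there corrects attenuation from slope error but does not restore lost precision.

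Finally, on the raw ratio that section 3.3 h) describes, the effect of t0 depends on the person's own level, so one common coefficient would be misspecified. That stands, and the remedy must fix the scale.

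**Conclusion.** The point holds as a low-cost efficiency improvement. The protocol collects a same-day t0 for every response, uses it only as normaliser, and lists primary models without it. The noise specific to each t0 sample therefore enters every slope undiluted.

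With k = 1, the gain at slope SD 3.7 is about 11 to 13 points at ρ = 0.5, 7 to 8 at ρ = 0.7 and 2 to 3 at ρ = 0.9. At SD 7.4 it is about 6, 3 to 4 and 1 points; at SD 11.1, about 3, 2 and 1. It falls to about 1 point or less in all three scenarios at k = 1.2 and ρ = 0.7 (at most 1.6), and to nil when ρk = 1. No single figure can be called the loss. The results rest on assumed ρ and k and on closed-form calibrations to the stated powers. They show neither bias in the planned analysis nor an error in the sample size statement.

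**What to change.** In section 4.1, state that the initial change is analysed as the log ratio of t1 to t0 (or as a difference). Add to steps 1 to 3 one fixed covariate: same-day t0 on that same scale, as its deviation from the participant's own mean over the three test days. Centring keeps between-person differences in resting level, which may relate to age, tissue status or inflammation, out of the coefficient. Take the individual slopes for the secondary objective from this model.

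The cost is a sentence or two of text and one coefficient per biomarker model, with no new samples or visits. The downside is one degree of freedom and possibly no gain. The estimated coefficient will show which case applies: near zero means that normalisation alone was already sufficient.
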